## **Statistic Strategy**

The variables of interest will be analyzed using the software (Graph Pad Prism version 7.0) and initially evaluated for the normal distribution of data using the Shapiro-Wilk test considering  $n < 30$ . In the case of data with normal distribution, they will be analyzed for the mean and standard deviation. Data without normal distribution will be analyzed for median and percentiles. Comparison analyses of the physical functional variables of the 30CST, MRI morphological variables, and HRV cardiac functional variables of the PRE-CR and POST-CR times of each group will be performed using the Wilcoxon test if the data were non-parametric and the paired t-test if the data were parametric. Comparison between the control and intervention groups for CPET will be performed using the independent t-test or the Mann-Whitney test, depending on the normality of the data. The reliability and validity of the 30CST will be analyzed using Spearman's correlation and the intra-examiner reliability coefficient. For all hypothesis tests, a significance of 5% probability ( $P < 0.05$ ) of error will be assigned.

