## **STUDY OBJECTIVES**

### **Primary objective**

To evaluate the efficacy and safety of early CR after AMI and its effect on physical fitness, morphology, and cardiac function.

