### **Secondary objectives**

- To assess the variation in functional capacity by measuring cardiorespiratory fitness after in-hospital CR, using maximum VO2 (maximum oxygen consumption) as a result measure;
- To analyze the dose of aerobic training provided to patients in in-hospital CR and its impact on the outcome of functional capacity;
- Relate the standard method of measuring VO2, the cardiopulmonary test, to a submaximal evaluation method, the 30s sit-to-stand test, evaluating its validity and reproducibility;
- Observe the influence of early CR on the morphological parameters of ventricular remodeling through nuclear magnetic resonance (NMR);
- Investigate heart rate variability after early cardiac rehabilitation.
- Identify the rate of adverse events and the safety level of the protocol evaluated in this clinical trial;

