## MATERIAL AND METHOD

### Study Design

This is a clinical trial protocol, controlled, randomized, single-blind with two groups, an allocation ratio of 1:1, and a hypothesis of superiority that will be carried out with patients admitted to the adult Intensive Care Unit (ICU) of the University Hospital Onofre Lopes (HUOL) with the clinical diagnosis of acute myocardial infarction. Figure 1 represents the follow-up flowchart of the study according to CONSORT (Consolidated Standards of Reporting Trials) (49). Figure 2 presents the flowchart with the main stages of the study.

[figure not shown]

**Fig. 1** – Study flowchart according to the Consolidated Standards of Reporting Trials (CONSORT).

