In step 2, patients will follow early exercise-based cardiac rehabilitation performed following all prescription parameters (FITT-VP) and safety criteria recommended by ACSM, 2018 (33). The institutional protocol (**Appendix B**) will be performed with a **frequency** of 2 sessions per day, during the entire hospitalization, with an average of 8 to 10 total sessions; Low **intensity** for aerobic training with METs estimated by the subjective perception of effort of BORG between 9 to 12 reaching between 2 to 3 METs and for resistance training with 2 to 3 series of 60% of the maximum repetitions reached in the 30s sit-to-stand test; **Type** of exercises involved will be aerobic training using the cycle ergometer associated with resistance training using the body's own weight with functional sit-to-stand training; Aerobic training **time** ranging from 3 to 20 minutes. The **Volume or Dose** of aerobic training will be measured by calculating the training dose per session and the total dose applied during hospitalization, providing a value in time x intensity (METs) x frequency of accumulated sessions and total number of sessions x time. The structured **progression** in the protocol focuses on the time of aerobic exercise and the number of series of resistance training. The exercise sessions will follow the protocol presented, however, present individualized prescriptions based on tolerance time during aerobic training with a cycle ergometer and resistance training from the maximum number of repetitions reached in the 30s TSL evaluated

individually before randomization.

Before hospital discharge, patients in the intervention group will receive an exercise guidance booklet (Appendix C) to perform step 3 of semi-supervised and continued cardiac rehabilitation with the exercise time reached at the end of in-hospital rehabilitation, frequency of 5 x per week and progression of 5 minutes each week within the first month after hospital discharge, according to tolerance and self-monitoring of intensity through perceived exertion using the Borg scale, maintained between 9 to 12, to ensure light exercise to moderate intensity. In this phase, patients in the intervention group will be monitored weekly by telephone and will receive a diary (Appendix C) to record the time of daily and weekly activity that they must deliver when investigating when they return for reassessment 30 days after hospital discharge.

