
**Fig. 4 – Cardiac rehabilitation unit – CPET (CORE-HUOL).**

### *30 second chair sit-to-stand test - 30CST*

The 30-second chair sit-to-stand test is a submaximal test indicated and validated for more debilitated individuals such as the elderly or hospitalized patients (30,31). In order to carry out the test, we will use, in accordance with previous studies and standardized recommendations, a rigid chair, with a standard height of 45cm and without armrests. The patient will be instructed to perform as quickly as possible in a time of 30 seconds the movement of sitting and standing up from the chair, which will be accounted for by the evaluator. The 30CST will be performed in 2 moments: At ICU discharge and 30 days after hospital discharge in both study groups.

The assessment of the intra- and inter-examiner reliability of the 30s TSL in post-AMI patients will be carried out from the recording of participants performing the TSL30s and evaluators previously selected to score the filmed tests. The total sample of 24 participants will be evaluated. The test will be administered by the principal investigator who will be blinded to the allocation of participants to study groups. Ten evaluators will be recruited from the hospital's team of physiotherapists from the ICU units and wards. All raters will be previously trained by the principal investigator before the assessments. After performing and filming the tests at ICU discharge (First assessment), the filmed tests will be presented to the evaluators who will score

each test. After 30 days, the same filmed tests will be presented again to the same evaluators for reassessment.

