### *Heart Rate Variability – HRV*

Heart rate variability (HRV) is an easy and non-invasive method to assess the integrity and functioning of the autonomic nervous system on heart rhythm. HRV can be observed by R-R intervals and its reduction is usually related to aging and worse health conditions (42,44,45).

In this research, the HRV will be measured before the randomization of the groups and at the outpatient return 30 days after hospital discharge using a Polar chest strap type heart rate monitor, model H10. The data provided by the heart rate monitor will be analyzed using Kubios HRV software. Variables of interest include those in the time domain: SDNN - standard deviation of all normal RR intervals recorded in a time interval, expressed in ms; pNN50 - represents the percentage of adjacent RR intervals with a duration difference greater than 50 ms. In addition to these variables, those in the frequency domain will be analyzed: High frequency component (HF) ranging from 0.15 to 0.4 Hz; Low frequency (LF) component, ranging from 0.04 to 0.15 Hz and the LF/HF ratio (45).

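### 30CST, MRI and HRV are tested only before versus after within each group, so the stated analysis of this randomised superiority trial cannot isolate an effect of early rehabilitation on them

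*Protocol*

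**What the plan says.** The Protocol's Study Design section describes two randomised groups with "an allocation ratio of 1:1, and a hypothesis of superiority". The Primary objective is "To evaluate the efficacy and safety of early CR after AMI and its effect on physical fitness, morphology, and cardiac function". Among the Secondary objectives are "Observe the influence of early CR on the morphological parameters of ventricular remodeling" and an investigation of heart rate variability (HRV) after early CR.

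The Statistic Strategy then divides the outcomes by type of test:

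- **30CST, MRI and HRV.** The comparison is of "variables of the 30CST, MRI morphological variables, and HRV cardiac functional variables of the PRE-CR and POST-CR times of each group", using the paired t-test or, for non-normal data, the Wilcoxon test.
- **CPET.** "Comparison between the control and intervention groups for CPET will be performed using the independent t-test", or the Mann-Whitney test for non-normal data.

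The only other analysis given for the 30CST concerns its reliability and validity. No section of the Protocol gives a between-arm test for 30CST, MRI or HRV.

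The measurements that such a test needs are already planned. For the sit-to-stand test, "The 30CST will be performed in 2 moments: At ICU discharge and 30 days after hospital discharge in both study groups". For HRV, "the HRV will be measured before the randomization of the groups and at the outpatient return 30 days after hospital discharge". The Abstract says that both groups undergo the same assessments, MRI and HRV included. The Cardiac morphology section places the baseline MRI around the fourth to sixth day after infarction, with two follow-up scans.

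**The concern.** Patients can be expected to change in the weeks after an infarction treated by PCI, whether or not they exercise. A control group exists so that this change can be subtracted. A paired test inside the CR arm does not subtract it, and a paired test inside the control arm tests only whether control patients changed. Two such tests side by side are not a test of the difference between arms.

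Followed as written, the plan would allow a change in ventricular volume, HRV or chair-stand count in the CR arm to be reported as an effect of CR when both arms changed equally. For these outcomes the randomised comparison would play no part in the inference.

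This is not a detail left open for a later analysis plan. The Protocol states the variables, the contrast and the tests, and the contrast is the wrong one for the objective. The split may follow the number of measurements. CPET is described as a measurement made after CR, and the Appendix A form has only a second-assessment field for it, whereas the other outcomes have a before and an after value.

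**Working it through.** **What each contrast estimates.** Let the mean natural change be m in both arms and the CR effect be e.

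- Change in the CR arm: m + e. The paired test asks whether m + e = 0.
- Change in the control arm: m. The paired test asks whether m = 0.
- Difference between arms: (m + e) − m = e. Only this contrast addresses the objective.

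**Inputs from the Protocol (Sampling and Recruitment; Statistic Strategy).** 12 per arm planned; 30% loss allowed; significance level 5%. Sidedness is not stated, so two-sided is assumed. After 30% loss, 12 × 0.7 = 8.4, so about 8 per arm. The Protocol has no figure of its own on this point to reproduce. Its sample size rests on VO2 and gives neither the mean difference nor the SD.

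**Assumptions.** The Protocol gives no size for natural change. I take m = 0.3, 0.5 and 0.8, in units of the SD of the change score, equal in both arms, with e = 0 and normal change scores.

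**Rejection by the CR-arm paired t-test.** The probability is that of |T| exceeding t(0.975, n − 1), where T is noncentral t with n − 1 degrees of freedom and noncentrality m × √n.

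| Natural change m | n = 12: m√n | n = 12: significant | n = 8: m√n | n = 8: significant |
|---|---|---|---|---|
| 0.3 SD | 1.04 | 15.8% | 0.85 | 11.4% |
| 0.5 SD | 1.73 | 35.3% | 1.41 | 23.2% |
| 0.8 SD | 2.77 | 71.4% | 2.26 | 49.6% |

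A simulation of 40,000 trials per setting agrees: 15.7%, 35.4% and 71.1% at 12 per arm, and 11.5%, 23.3% and 49.6% at 8. In the same simulated trials a between-arm t-test of change rejects in 5.0% to 5.2% at 12 per arm and 4.9% to 5.1% at 8, whatever the natural change. At 1.0 SD the CR-arm rejection rate rises further, to 88% at 12 per arm and 68% at 8.

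**Wilcoxon route.** With exact critical values and 100,000 simulated arms, the CR-arm test is significant in 13.7%, 31.8% and 66.7% at 12 per arm, and in 9.2%, 19.3% and 43.1% at 8. The choice between the two paired tests does not alter the conclusion.

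**Precision of the between-arm comparison.** The 95% CI half-width for a difference in mean change is t(0.975, 2n − 2) × √(2/n):

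- n = 12: 2.074 × 0.408 = 0.85 SD
- n = 8: 2.145 × 0.500 = 1.07 SD

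**The case against.** The strongest reply concerns weight. The trial is sized on VO2, and CPET does have a between-arm test. MRI and HRV are also listed under Secondary objectives in exploratory terms. That moderates the point without removing it, because the Primary objective itself names morphology and cardiac function and the design is declared a superiority trial. A second reply is that a between-arm test of change is implied. The wording does not allow this: the named tests are paired, they apply to each group, and the group comparison in the next sentence is confined to CPET.

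A third reply is that baseline adjustment is not clean for MRI. This stands. Randomisation follows recovery of functional mobility (Early cardiac rehabilitation program), so a scan around day 4 to 6 may come after it, and adjustment or a change score could absorb a small early CR effect. The remedy has to allow for that. HRV does not share the problem, since its baseline precedes randomisation, and the program section also places the individual sit-to-stand assessment before randomisation.

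Some stronger readings are tempting but not supported.

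- **The 3-month MRI has no analysis.** A reader might infer this because 30CST and HRV are repeated at 30 days and the intervention group's home diary is handed in "when they return for reassessment 30 days after hospital discharge". But POST-CR is not defined, the paired test could be run at each follow-up scan, the timeline figure is not shown, and choosing among follow-up times can be left to an analysis plan.
- **The plan will call an effect whenever CR is significant and control is not.** The Protocol states no such rule. Nor does the pattern keep growing with natural change: at 12 per arm and 1.0 SD it is 0.883 × 0.117, about 10%.
- **Harm from training would be hidden.** The control arm is tested too, so a change there alone would be displayed, though not validly compared.
- **A fixed number of false findings can be counted.** The Statistic Strategy names one test and two classes of variable, and the Cardiac morphology section gives volumes and ejection fraction only as examples.

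**Conclusion.** The point holds for the stated contrast and should be corrected. For 30CST, MRI and HRV the Protocol fixes a within-group test that cannot separate a CR effect from natural change after infarction, and nothing elsewhere in it repairs this. Under no CR effect and an assumed equal natural change of 0.3 to 0.8 SD, the CR-arm t-test is significant in 16% to 71% of trials at 12 per arm and 11% to 50% at 8, where a between-arm test of change holds 5%. Those percentages rest on the assumed natural change and on normal data. The conclusion that the contrast is wrong rests on neither. It does not extend to CPET, for which a between-arm test is given.

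**What to change.** In the Statistic Strategy, make the main analysis of 30CST, HRV and MRI a comparison between arms. Preferably, compare follow-up values adjusted for the baseline value. At minimum, apply the independent t-test or Mann-Whitney test already named for CPET to change from baseline. Give each difference with a 95% CI, and keep within-group changes as description only. For MRI, also report the unadjusted between-arm difference at follow-up, because the baseline scan may come after randomisation.

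The cost is a few sentences and slightly more analysis work. The measurements are already scheduled in both arms. The visible downside is wide intervals, with half-widths of about 0.85 SD at 12 per arm and 1.07 SD at 8. That imprecision comes from the sample size, and reporting it is more informative than a within-arm p-value that does not address the question.

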### Cardiac morphology and function analysis

#### Cardiac morphology

Cardiac nuclear magnetic resonance (NMR) can be used for several important evaluations after acute myocardial infarction. MRI allows the diagnosis of myocardial infarction in its acute or chronic condition, provides several prognostic indicators that can impact the risk stratification of patients, in addition to allowing the identification of complications after AMI, such as aneurysm, pericarditis, and thrombi among others (53). The evaluation of the extent of scarring after AMI is a valuable predictor of therapeutic success, being used as a common endpoint in clinical trials. The extent of infarction is inversely related to clinical prognosis and is a more sensitive predictor than mass and ventricular ejection fraction of ventricular tachycardia, ultimately predicting all-cause mortality and ejection fraction-independent survival (53).

In this study, standard protocols will be used to assess cardiac morphology and function, such as end-systolic and diastolic volumes and ventricular ejection fraction evaluated through the CINE SSFP sequence, in addition to the delayed enhancement sequence with gadolinium (53). The exam will be performed at baseline, still during hospital stay, around the fourth to sixth day after the AMI and in two follow-up moments, the first one from 4 weeks after the event, with a tolerance of up to 2 weeks for image and the second from 3 months after the event with a tolerance of two weeks.

The technique used to evaluate the scar extension will be the delayed enhancement with the administration of gadolinium chelate. The patient will receive the gadolinium chelate between 10 and 20 minutes before the exam. In the presence of scar tissue, there is an increase in the extracellular space in relation to the intracellular environment due to the rupture of the cardiomyocyte membranes, with greater gadolinium impregnation in this region, generating hyper-enhancement in the image (53). Scar size assessment will use the following semi-quantitative method: Visual scoring of 17 standardized areas, on a 5-point scale, where 0= no hyperenhancing, 1= 1-25%, 2= 26 – 50%, 3=51

– 75% and 4= 76 – 100% hyperenhancing. The total scar score is given by adding the

scores for each segment and dividing by 17 (53).

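### 30CST, MRI and HRV are tested only as pre/post change within each arm, so morphology and cardiac function have no test of CR against control

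*Protocol*

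**What the plan says.** The Study Design section describes a randomised trial with "an allocation ratio of 1:1, and a hypothesis of superiority". The primary objective is "To evaluate the efficacy and safety of early CR after AMI and its effect on physical fitness, morphology, and cardiac function". The secondary objectives include the influence of early CR on MRI remodelling parameters and on heart rate variability.

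The Statistic Strategy assigns tests by outcome:

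- **30CST, MRI and HRV:** "MRI morphological variables, and HRV cardiac functional variables of the PRE-CR and POST-CR times of each group will be performed using the Wilcoxon test". The stated alternative is "the paired t-test if the data were parametric".
- **CPET:** "Comparison between the control and intervention groups for CPET will be performed using the independent t-test or the Mann-Whitney test".
- **All tests:** "For all hypothesis tests, a significance of 5% probability".

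The 30CST also gets a correlation and a reliability coefficient. Neither compares the arms.

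MRI is done at baseline, around day four to six after the infarction, and then "in two follow-up moments, the first one from 4 weeks after the event", with the second from three months.

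**The concern.** A paired test inside one arm asks whether patients in that arm changed. A superiority hypothesis asks whether the CR arm changed differently from control. The Statistic Strategy asks only the first question for 30CST, MRI and HRV.

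Baselines are taken days after an infarction, and follow-up comes weeks to months later. Both arms have had PCI and receive drug treatment and early mobilisation. Change over that period without further CR is plausible, in either direction. A within-arm test adds that change to any CR effect and cannot separate the two. Setting the two within-arm p-values side by side does not help, because two arms with identical true change will often fall on opposite sides of 5% by chance.

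At stake are the conclusions on ventricular remodelling and autonomic function, which are stated aims. They would rest on comparisons that make no use of the randomisation.

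**Working it through.** **1. What kind of test is fixed.** Wilcoxon alone could mean the rank-sum test between groups. The parametric alternative for the same outcomes is the paired t-test, and the comparison is of pre and post times in each group, so the signed-rank test is meant. The next sentence names the independent t-test and Mann-Whitney test, for CPET only. The protocol thus uses both kinds of test and gives these three outcomes the within-arm kind.

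**2. Objectives set against tests.**

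| Objective | Test of CR against control |
|---|---|
| Primary: physical fitness | Yes, through CPET |
| Primary: morphology | None |
| Primary: cardiac function | None |
| Secondary: maximum VO2 | Yes (CPET) |
| Secondary: MRI remodelling | None |
| Secondary: HRV | None |
| Secondary: 30CST validity and reproducibility | Not a treatment-effect objective |

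**3. Size of the misreading risk.** The plan gives no figure of its own to reproduce here.

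Inputs from the protocol: 12 per group and a 30% loss allowance (Sampling and Recruitment), which leaves 12 × 0.7 = 8.4, taken as 8 per group; significance level 5%.

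Assumptions: two-sided tests (sidedness is not stated), no CR effect, independent arms, the same true change in both arms, normally distributed changes. The size of the common change is d, the mean change divided by the SD of change. The documents give no value, so a range is shown.

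Formulas: the paired t statistic has n − 1 degrees of freedom and noncentrality d√n. The chance p that one arm is significant is P(|T| > c), where c = 2.201 for n = 12 and 2.365 for n = 8. The chance that the CR arm alone is significant is p(1 − p), which cannot exceed 25%.

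Example, n = 12 and d = 0.5: noncentrality 0.5 × √12 = 1.732, p = 0.353, p(1 − p) = 0.353 × 0.647 = 0.228.

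| d | n = 12: CR arm significant | n = 12: CR arm alone | n = 8: CR arm significant | n = 8: CR arm alone |
|---|---|---|---|---|
| 0.2 | 10% | 9% | 8% | 7% |
| 0.3 | 16% | 13% | 11% | 10% |
| 0.5 | 35% | 23% | 23% | 18% |
| 0.8 | 71% | 20% | 50% | 25% |
| 1.0 | 88% | 10% | 68% | 22% |
| 1.2 | 97% | 3% | 83% | 14% |

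The columns for the CR arm being significant are the power to detect a change that is real under the assumption. They are not error rates, but such a result could be misread as a CR effect. The columns for the CR arm alone give the chance of a pattern that would be wrong if read as CR beating control. A between-group test of change has a 5% false-positive rate at every value of d, because the common change cancels.

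**4. MRI time points.** A pre/post test needs one post value, and two follow-up scans are planned. The Statistic Strategy does not say which is POST-CR. The clinical evaluation form (Appendix A) has lines for only two scans in all.

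**The case against.** **The main outcome is sound.** The sample size rests on maximum VO2, and CPET has a between-group test. This stands. A reader might infer that the trial has no valid comparison, or that most of its objectives lack one. The documents do not support that: fitness is covered through CPET, and the listed 30CST objective concerns validity and reproducibility. The gap is in morphology and cardiac function, which the primary objective names equally.

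**The details may be in an analysis plan.** A protocol may leave detail to such a plan. Here it states the tests itself, and they are within-arm tests, so this does not answer the point.

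**The control arm is still there to look at.** Its change would be visible, but without an estimate or test of the difference it does not protect the inference.

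**The figures depend on assumptions.** This stands. A reader might take 71% or 88% as false-positive rates. They are not. Nor does the protocol state a rule that declares CR effective when only its arm is significant, so the smaller percentages apply only if results are read that way. They also fall again when the common change is large.

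**Change need not be recovery.** This also stands. The introduction describes remodelling after infarction as something that can lead to dysfunction, so the shared MRI drift could run either way. The argument needs only change over time.

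**MRI.** A reader might infer that one follow-up scan is discarded. The text does not say so, since baseline could be paired with each follow-up. What it supports is that POST-CR is undefined for MRI.

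**Conclusion.** The stated analysis is wrong for its purpose. For 30CST, MRI and HRV the protocol fixes only within-arm tests, which do not answer a superiority question. Two of the three primary-objective domains, and the MRI and HRV secondary objectives, are left without a test of CR against control. This follows from the text and rests on no assumed number.

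The size of the risk does rest on assumptions. With no CR effect and equal change in both arms, the CR arm alone is significant in up to 23% of trials at the tabulated values with 12 per arm, and up to 25% with 8. The figure falls to 3% and 14% at the largest change shown. The CPET comparison and the sample size are not affected. This should be corrected before analysis.

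**What to change.** In the Statistic Strategy, make the comparison between arms the inferential analysis for 30CST, HRV and MRI.

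- **30CST and HRV:** compare the 30-day value between arms, adjusted for the pre-randomisation value (ANCOVA), and report the adjusted mean difference with its 95% CI. At minimum, compare change scores between arms with the independent t-test or Mann-Whitney test already planned for CPET.
- **MRI:** state which follow-up scan is POST-CR and compare arms at each of the two follow-ups. A mixed model covering both is optional.
- **Within-arm change:** report descriptively, without p-values.

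The cost is a few sentences and a little more analysis work, and for ANCOVA possibly other software. No new data are needed: the abstract says both groups undergo the same assessments. The corrected analysis will also show how little a trial of this size can detect. A two-sided between-group t-test has 80% power only for a standardised difference of about 1.20 with 12 per arm, or 1.51 with 8, so the confidence intervals should carry the interpretation.

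### The 30CST analysis sentence names no inter-examiner statistic, assigns no statistic to each aim, and leaves the form's 30-minute repeat test unused

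*Protocol*

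**What the plan says.** Four places in the protocol bear on this point.

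- **Secondary objectives.** The protocol will relate VO2 from the cardiopulmonary test to "the 30s sit-to-stand test, evaluating its validity and reproducibility".
- **30 second chair sit-to-stand test section.** "The assessment of the intra- and inter-examiner reliability of the 30s TSL in post-AMI patients will be carried out from the recording of participants", scored by several raters: "Ten evaluators will be recruited from the hospital's team of physiotherapists from the ICU units and wards". On numbers, "The total sample of 24 participants will be evaluated". For the second reading, "After 30 days, the same filmed tests will be presented again to the same evaluators for reassessment". This section has the test done on two occasions, ICU discharge and 30 days after hospital discharge.
- **Statistic Strategy.** The only analysis text for this objective is one sentence: "The reliability and validity of the 30CST will be analyzed using Spearman's correlation and the intra-examiner reliability coefficient".
- **Appendix A, Physical tests.** The form has four 30CST entries: one at each assessment, and a further one 30 minutes after each. It has one CPET entry, at the second assessment.

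**The concern.** The design section plans two kinds of rater reliability and the analysis sentence covers one. Followed as written, the inter-examiner question is either not analysed or falls to Spearman's correlation, the only other statistic named. Spearman's correlation depends on rank order alone, so a rater who always counts two more than a colleague looks perfect.

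Absolute counts matter here. The early rehabilitation programme sets sit-to-stand training at 60% of the repetitions reached in this test, so a 2-repetition offset moves the prescribed set by 0.6 × 2 = 1.2 repetitions.

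Reproducibility is a separate gap. Re-scoring a recording shows whether a rater counts the same film the same way twice. It does not show whether a patient would give the same result on a second attempt. Only the 30-minute repeat on the form could show that at short interval, and neither the procedures nor the analysis mentions it.

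At stake is a published statement that the 30CST is reliable and reproducible after AMI, resting on statistics that do not address part of it.

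**Working it through.** The protocol gives no sample size, target or expected value for reliability, so there is no stated figure to reproduce. The check has two parts.

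**1. Aims set against statistics**

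| Aim in the protocol | Data planned | Statistic named |
|---|---|---|
| Validity against VO2 | 30CST and CPET at the second assessment | Spearman fits, but is not assigned |
| Intra-examiner reliability | Same raters, same films, two scorings | Intra-examiner coefficient, type undefined |
| Inter-examiner reliability | 24 films × 10 raters | None |
| Reproducibility of performance | 30-minute repeats, on the form only | None |

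**2. What the named statistics can and cannot detect**

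From the protocol: 24 films, 10 raters. Assumptions, because the protocol gives none: between-patient SD of 3 repetitions (range 2 to 4), and the offsets between raters shown below.

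For two scorings that differ by a constant s with no random error, the rater variance is s²/2, and

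ICC (absolute agreement, single measure) = SD² / (SD² + s²/2).

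- SD 3, s = 2: 9 / (9 + 2) = 0.82
- SD 3, s = 3: 9 / (9 + 4.5) = 0.67
- SD 2, s = 3: 4 / (4 + 4.5) = 0.47
- SD 4, s = 3: 16 / (16 + 4.5) = 0.78

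Spearman's rho is 1.00 in every one of these cases.

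With random counting error added (SD 3, error SD 0.7, counts rounded, n = 24, simulated), rho stays at about 0.92 for offsets of 0, 1, 2 and 3. The absolute-agreement ICC falls from 0.94 to 0.88, 0.76 and 0.63.

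For the intra-examiner coefficient, take ten raters who each repeat themselves exactly but carry fixed biases with SD b. Even an intra-examiner coefficient in ICC form is then 1.00 throughout. The inter-examiner ICC is about 9 / (9 + b²):

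- b = 1: 9/10 = 0.90 (simulated 0.90)
- b = 2: 9/13 = 0.69 (simulated 0.70)

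So neither named statistic, however favourable, answers the inter-examiner question.

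**The case against.** The strongest reply is that the sentence covers reliability and validity together and names two statistics. The natural reading gives correlation to validity and the coefficient to reliability. The coefficient may well be an intraclass correlation, which in absolute-agreement form does measure agreement within a rater, and its exact form can be left to an analysis plan. Most of this stands. A reader might infer that the protocol uses Spearman to prove agreement, or that neither named statistic can show agreement. The text supports neither inference: Spearman is not expressly assigned to agreement, and the coefficient is undefined, not wrong. What the reply does not supply is any statistic for the inter-examiner half of the protocol's own design.

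A reader might also infer that the arms will be pooled in the 30CST–VO2 correlation, so that a treatment effect on both measures creates correlation. With no within-arm correlation and a 1.5 SD effect on both, the pooled value would be (1.5²/4) / (1 + 1.5²/4) = 0.36. About 1.5 SD can be worked back for VO2 from 7 per group at 80% power and two-sided 5%. For the 30CST the protocol gives no effect, and nowhere does it say that the arms will be pooled. This is a reason to specify the adjustment, not an error in the text.

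It is also tempting to predict near-perfect film scores. Nothing in the protocol supports that prediction, and it sits badly with offsets of 2 or 3 repetitions. Raters are trained and watch the same recordings, so the real offsets may be small, and the choice of statistic would then matter less.

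Finally, the form does not say what the 30-minute repeat is for; it could be familiarisation or best of two. Two occasions might also be read as two visits. Either way, the repeat is undescribed in the procedures and has no stated use.

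**Conclusion.** The point holds in a limited form. The firm part is an internal mismatch: inter-examiner reliability is planned with ten raters and has no analysis. The sentence also leaves the statistics unassigned and the coefficient undefined. The form's four 30CST entries do not match the two occasions in the procedures, and the repeats are unused although reproducibility is an objective.

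The size is illustrative. At an assumed between-patient SD of 3, a constant offset of 2 or 3 repetitions gives an absolute-agreement ICC of 0.82 or 0.67 while rho stays at 1.0. Over SDs of 2 to 4, a 3-repetition offset gives 0.47 to 0.78. These figures show what would be missed if raters differ systematically; they do not predict that they will.

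This should be changed, but it touches one of six secondary objectives and not the treatment comparison, the sample size or the safety assessment.

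**What to change.** Replace the single sentence with one line per aim.

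1. **Validity:** correlation only, 30-day 30CST against 30-day peak VO2, with 95% CI. Adjustment for arm is preferable (partial correlation), because CPET is measured only after treatment.
2. **Inter-examiner reliability:** two-way random-effects, absolute-agreement, single-measure ICC with 95% CI and standard error of measurement, on 24 films × 10 raters.
3. **Intra-examiner reliability:** the same ICC and standard error of measurement on the two scorings 30 days apart.
4. **Reproducibility:** reconcile Appendix A with the 30CST section. If the 30-minute repeats are kept, describe them in the procedures, state their purpose, and analyse them as test-retest with the same ICC and standard error of measurement. If they are dropped, limit the conclusion to rater reliability.

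Items 1 to 3 use data already planned. Item 4 needs the form and the procedures to be aligned first. The cost is a little more analysis work and possibly less favourable reliability figures than a rank correlation would give.
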